#### Adolescent screening

With formal parental consent obtained, we directly reach out to the adolescents, within the time windows and using the method preferred by the parent. Although this initial interaction begins the assent process, it also verifies adolescents’ willingness to have a study team member contact them directly.

On every call with adolescents, before launching into the agenda for the call, we check in with the adolescent about their privacy, encouraging use of earbuds or headphones. If any such concerns surface during the call, the researcher shifts the agenda to finding a time to reschedule the call.

When the privacy assessment is complete, we explain the purpose of the study and the adolescent’s central role in it. We describe the three types of data we are using (survey, interview, and administrative records) and our expectations of families who agree to participate. We offer an opportunity for adolescents to ask any questions.

Finally, we explain how the consent process works. Although we have already talked with their parent, we do not enroll the adolescent unless they want to participate. The adolescent must personally decide whether he or she wants to participate in the study, and the research team must respect that decision. If the adolescent is willing to participate, he or she will need to document that for us. In addition, their parent will need to document her or his permission for the adolescent to participate. Both the adolescent and the parent must agree before the adolescent may participate.

#### Consent and assent

We fully assent adolescents at the beginning of both data collection waves, initially, before they complete their first survey and interview and once again when it is time to complete the second one. When we administer consent or assent, we send the participant a link(s) to the appropriate form(s) and verify that she or he has access. If needed, researchers offer to share a video screen displaying the consent documentation. We review study procedures and talk through the elements of consent as presented in the documents. Within that discussion, we verify their understanding of three types of data we will use in this study (interview, survey, and administrative records). We give all participants another opportunity to ask questions about the study. We also ask them questions to verify their comprehension of the elements of consent or assent. Finally, we ask them whether they are willing to consent to participate in this study, as described below. For both parents and youth, consent/assent is documented electronically in a procedure approved by the IRB. We document participants’ consent/assent by asking them to electronically sign the form HIPAA compliant study portal operated at Purdue.

#### Retention strategies

Evidence-based strategies [52] will be used to minimize attrition between interviews, with particular attention to strategies that have been shown to be effective with youth [53] including: careful attention to educating and motivating participants [54] prompt provision of incentives [55] and effective use of locater data.

#### Compensation

Prospective participants are given a small pre-incentive valued at $1.29. Those screened eligible for participation also are given a preincentive valued at $5 along with their study participation materials. For completing the first survey, each family member receives $15. For completing the first interview, each family member receives $20. Furthermore, when all family members have completed their baseline assessments they are sent a gift valued at no more than $12, which will be something family members can all share (e.g., gourmet popcorn). At the time of the second round of interviews, participants also are sent a gift valued at approximately $5 (e.g., earbuds).

During the second wave of data collection, each family member will be compensated $20 for survey completion and $30 for interview completion, all subject to military regulations for active service members. Compensation will be sent via a separate check for each participant following the completion of each wave. When all family members have completed their second and final wave of data collection, each family member will be sent a project-specific "challenge coin." Each coin costs approximately $7 but has no cash value.

### Data collection procedures

After formal consent/assent is complete, data collection begins immediately. Participants are promptly be sent a link to complete the web-based survey. To facilitate privacy when completing sensitive questions (e.g., perceptions of their relationships with their partner or parents), these surveys are compatible with computers or mobile devices (i.e., tablets and smartphones).

Survey completion requires an internet connection. When this poses a problem, the survey is administered in interview format over the telephone. Interviewers conduct interviews using scripts and prompts built into the interview form and enter participants’ responses directly into Qualtrics’ FedRAMP-compliant data system.

We conduct interviews separately with each participant in a private setting. To establish trust and rapport with the interviewer, we encourage a video connection, but we do not require the participant to have (or use) a camera. If needed, we are prepared to conduct interviews over the telephone. Interviews last approximately 60 minutes for parents and 45 minutes for adolescents and comprise mostly closed-ended questions. We provide participants with response cards: colored cards containing each unique response set that are used in the interview (e.g. 1 = ‘no’, 2 = ‘yes’; 1 = ‘strongly disagree’ to 5 = ‘strongly agree’). Response cards allow participants to answer with symbols instead of words to protect privacy and assist with transitions between sections of the interview when the interviewer references the color needed for the next section.

We provide response cards in electronic format, compatible with tablets and smartphones. To help protect privacy, colors for adolescents are associated with different responses than for adults. Furthermore, when using electronic response cards, adolescents can answer sensitive questions directly on the response cards. When interviewing adolescents, the interviewer and adolescent agree on a word or phrase to use if they want to skip a question, withdraw from the study, or if someone has entered the location where they are completing the interview and provoked a privacy concern.

### Administrative data and measures

Administrative data will be requested from the: **A)** Defense Enrollment Eligibility Reporting System (DEERS)–demographic and background information; **B)** Contingency Tracking System (CTS) and Personnel Tempo (PERSTEMPO)–deployment history data including locations, dates, and types of deployments; and **C)** Medical Data Repository (MDR)–health care utilization and diagnoses for each child and parent.

Measures (see Table 2) to be used for the collection of new data were selected to reflect mechanisms of both resilience and risk, and positive and negative youth outcomes in multiple domains. To support use of latent variables, multiple measures of each major construct were selected for age-appropriateness, established psychometric properties, brevity, and use with military populations and multiple ethnic groups. Measures with established norms or civilian community benchmarks were prioritized (e.g., National Survey of Drug Use and Health, Youth Risk Behavior Survey, National Survey of Children’s Health). Assigned sex of both parents and youth will be included in demographic questions but will be treated analytically as moderators per Aim 3 (sex is operationalized as male and female because of Department of Defense restrictions in place at the time of study approval). Race and ethnicity will be operationalized in accordance with U.S. Office of Management and Budget Guidelines (Office of Management and Budget (OMB) Standards | Office of Research on Women’s Health (nih.gov)). Guided by a family risk and resilience framework, the outcomes of interest will be each child’s social-emotional, behavioral, and academic adjustment. The sequence of measures will be specified, but the order in which parents and children are asked about one another will be randomized to avoid order and fatigue effects.

**Table 2 pone.0295007.t002:** Measures to be administered and administrative data to be obtained.

	Measures by Respondent by Instrument	*Data Source*	
*Category / Construct*	*Measure / reliability / reference*	Parent	Youth

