This study also is designed to permit consideration of both parent and youth sex as moderators of the relationships between early exposure to parental deployments and later youth adjustment. There are good reasons to expect that mothers’ deployments may be especially impactful or that boys and girls may be differentially vulnerable, but existing evidence is mixed.

Consistent with Masten and Narayan’s [39] recognition that the developmental timing of adverse experiences is consequential, deployments, life events, and other experiences will be coded in ‘child time’ (i.e., months since birth), including exposures occurring prenatally, as well as timing relative to deployment. More positive outcomes are expected when exposures began later and were less frequent or prolonged, and/or when parents experienced fewer traumatic experiences during deployment. The controlled heterogeneity of deployment timing in this study will help to provide greater clarity about the role of child age in these effects, thus addressing the lack of consistency in previous findings in relation to deployment effects.

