**Background Characteristics**			
**1. Demographics**	All: Age, race/ethnicity; Parents: Income, work status, education completed, marital history	Survey	Survey
**2. Family structure**	Household and family structure; age, sex and living arrangements of children; (items asked depends on number of children).	Interview	
**3. Military status & history**	Dates, branch and component, pay grade;	Records	
**4. Civilian Employment**		Survey	
**5. Children’s health**	National Survey of Children’s Health [56]	Interview	
	Pubertal Development Scale(α = .78) [57]		Survey
**6. Personal characteristics**	Emotion regulation [58]	Survey	Survey
	Self-efficacy [59]	Interview	Survey

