### Model building and estimation

Measurement models will be developed first, per the psychometric analyses. Latent variables will be used when computationally possible. Structural models will be built in stages paralleling study aims, assessing model fit to the data at each stage [112]. Analyses will be conducted using AMOS, Mplus 7 [111], STATA [113], and SAS [114]. Item-missing data will be handled using Full Information Maximum Likelihood (FIML) procedures available within Mplus and STATA [115]^.^ This approach is advantageous, as simulation studies have found it performs superior to listwise deletion and multiple imputation [116]. Sampling weighted estimation that corrects for unequal selection and non-response across strata will be used [107, 117]. In general, an alpha of 0.05 will be used to determine support or lack thereof for hypotheses. However, focus will be on effect size and confidence intervals for the distribution of effects [118].

A mixed-effects modeling approach to the multilevel, nested data structure will be used to explicitly estimate within- and between-family variability [119]. Change in children’s outcomes will be evaluated with two types of models: 1) Three-level mixed-effect models with time nested within child and siblings nested within families, where change is assessed using a predictor variable indicating baseline and follow-up time points, and interactions with the time variable test the effects of predictors on changes in outcomes; and 2) Two-level models with siblings nested in families that include autoregressive effects for each outcome (i.e., control for Time 1 levels), thus controlling for stable levels of each construct and testing effects on residualized change. Both approaches to modeling change provide rigorous inferences about the hypothesized relationships [120]. Models will control for: 1) parents’ age, education, and minority and employment status; 2) family type and size; 3) military branch and paygrade. Sensitivity analyses will be conducted to ensure that these controls do not obscure important findings. Strategies for analyzing each aim are described below.

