#### Analyses for aim 1: To assess direct relationships between the timing, frequency, duration and content of siblings’ early exposures to parental deployments and later youth adjustment

Maladjustment is hypothesized to be greater for children whose exposures began earlier (operationalized as child age at first deployment, including gestational age, coded from archival data), were more frequent (i.e., total number of deployments during the child’s lifetime) prolonged (i.e., total days deployed), ended more recently (i.e., days since end of most recent deployment), or who were exposed to deployments where parents’ experiences were more traumatic (i.e., total scores on self-report Combat Exposure items). These hypotheses will be tested using a SEM framework, where a series of path models will estimate the direct effects of deployment characteristics on each indicator of adjustment. Paths from the independent variables will be tested concurrently, thus establishing the unique association for each deployment risk factor. Interactions between different deployment components—frequency, duration, timing, and content—will also be examined to determine whether long-term effects of deployment are exacerbated or mitigated for various deployment combinations. Within-family comparisons will be conducted to determine whether these direct effects differ across siblings.

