#### Analyses for aim 3: To assess the moderating role of parent and sibling sex, and vulnerability and support in relationship between siblings’ exposures to parental deployment and later youth adjustment

This aim identifies risk and protective factors that may amplify or dampen direct and indirect links between deployments and youth outcomes. Continuous moderators will be tested using procedures outlined by Preacher, Rucker, and Hayes [123]. Specifically, conditional indirect effects will be estimated, with the expectation that relationships between deployment and mediating variables will be stronger when parents experience greater vulnerability and less support, and that relationships between mediating and outcome variables will be stronger when youth experience greater vulnerability and less support. Multi-group analyses will be used to test categorical moderators (i.e., parent and child sex), using likelihood ratio (chi-square) tests to assess whether unconstrained models that allow groups to vary fit better than models constraining direct effects to be equal across groups [105].

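### Youth sex is reserved for Aim 3 moderation and missing from the stated controls, so the Aim 1 and 2 youth-outcome models give up a modest amount of precision that costs nothing to recover

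*Protocol article*

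**What the plan says.** Under Administrative data and measures, the protocol article gives sex its analytic role: "Assigned sex of both parents and youth will be included in demographic questions but will be treated analytically as moderators per Aim 3". Youth sex will be in hand: Table 2 lists "age, sex and living arrangements of children" under family structure, and the study overview lists children's genders among the DEERS variables.

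Model building and estimation gives one control list ahead of the strategies for the three aims: "Models will control for: 1) parents’ age, education, and minority and employment status; 2) family type and size; 3) military branch and paygrade". The next sentence adds: "Sensitivity analyses will be conducted to ensure that these controls do not obscure important findings".

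For Aim 1, "a series of path models will estimate the direct effects of deployment characteristics on each indicator of adjustment", with no further covariates named. The Aim 2 section names none either. Child sex first enters under Aim 3: "Multi-group analyses will be used to test categorical moderators (i.e., parent and child sex".

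Two other statements bear on the point. The sample size section expects power to rise when controls account for variance in mediators and outcomes. Model for the proposed study says that "boys and girls may be differentially vulnerable", while calling the existing evidence mixed.

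**The concern.** The outcomes are youth anxiety, depression, peer relations, problem behaviour, substance use and the like. If boys and girls differ on average on any of these, a model without youth sex treats the difference as unexplained error. Youth sex is a good covariate on general grounds: it will already be collected and is not a consequence of deployment, so adjusting for it carries no over-adjustment risk.

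The omission matters most for sibling comparisons, which the article presents as a main strength. Every listed control describes the parents, the household or the military career, and siblings largely share these. They can explain little of the variation within a family. Youth sex can: it differs between the two children in every brother-sister pair.

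What is at stake is the width of the confidence intervals for the Aim 1 and Aim 2 effects.

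**Working it through.** **Inputs from the protocol article (sample size section and Table 1).** 712 families with 2 children each, within-family ICC 0.30, alpha 0.05, power 0.80. Cross-sectional detectable standardized betas are 0.085 (family-level) and 0.063 (child-level).

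**Inputs assumed.** A boy-girl difference of d = 0.2 to 0.5 SD, equal numbers of boys and girls, siblings' sexes independent, and sex unrelated to exposure. The documents give no value for d.

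**Step 1: reproduce Table 1.** With two-sided alpha, the multiplier is 1.960 + 0.842 = 2.802.
- Family level: effective n = 2 × 712 / (1 + 0.30) = 1,095; beta = 2.802 / √1,095 = 0.0846, stated 0.085.
- Child level: effective n = 1,424 / (1 − 0.30) = 2,034; beta = 2.802 / √2,034 = 0.0621, stated 0.063.

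All 12 effective sample sizes in the table reproduce to rounding, and all 12 betas agree to within 0.001.

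**Step 2: variance explained by sex.** R² = d² / (d² + 4).
- d = 0.2: 0.04 / 4.04 = 0.0099
- d = 0.5: 0.25 / 4.25 = 0.0588

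**Step 3: where that variance sits.** Total variance is set to 1, with 0.30 between and 0.70 within families. If siblings' sexes are independent, the sex component adds nothing to the sibling covariance, so it lies wholly in the 0.70. A family mean over two children has variance 0.30 + 0.70/2 = 0.65, of which sex supplies R²/2.

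**Step 4: effect of adding youth sex.** The SE ratio is the square root of the residual-variance ratio. Power is Φ(2.802 / SE ratio − 1.960), starting from 0.80.

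| | d = 0.2 | d = 0.5 |
|---|---|---|
| Child-level residual | 0.70 → 0.690 | 0.70 → 0.641 |
| Fall in variance | 1.4% | 8.4% |
| Fall in SE | 0.7% | 4.3% |
| Power | 0.806 | 0.833 |
| Detectable beta (from 0.063) | 0.0626 | 0.0603 |
| Family-level residual | 0.65 → 0.645 | 0.65 → 0.621 |
| Fall in variance | 0.8% | 4.5% |
| Fall in SE | 0.4% | 2.3% |
| Power | 0.803 | 0.818 |
| Detectable beta (from 0.085) | 0.0847 | 0.0831 |

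**Step 5: which models this covers.** The table describes effects on the level of an outcome at one occasion.
- *Three-level models, predictor-by-time interaction.* With two waves these tests rest essentially on differences within a child, from which a constant sex main effect cancels. The gain is close to nil.
- *Two-level autoregressive models.* The Time 1 outcome already absorbs much of any stable sex difference. The gain is smaller than tabulated; the documents give no correlation over time with which to size it.
- *Binomial and other non-linear outcomes.* The gain appears as test power, not necessarily as a smaller standard error.

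**The case against.** The strongest reply is that nothing is formally excluded. The article assigns sex to moderation without saying that it has no other use, the control list is a one-sentence summary in a condensed article, and a fuller specification may exist elsewhere. That is fair as to intent. Even so, the article prints an explicit list and sets sex apart from it in a separate sentence, and neither the Aim 1 nor the Aim 2 section brings it back. The promised sensitivity analyses ask whether the listed controls hide findings; they do not add a control.

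A second reply is that the Aim 3 multi-group models by child sex already account for the boy-girl difference, because only direct effects are described as constrained across groups. That holds within Aim 3. The pooled Aim 1 and Aim 2 estimates, which carry the main hypotheses, remain unadjusted.

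A third reply is that the gain is small and rests on an assumed input. This stands. The remark that boys and girls may be differentially vulnerable concerns the deployment effect, not a mean difference in outcomes, so it does not support any value of d. The article also cites betas of 0.18 to 0.32 for recent deployment, above every detectable value in Table 1 (largest 0.139).

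A reader might infer that chance imbalance between sex and age at exposure biases the sibling contrasts. The documents do not support that. If sex is unrelated to exposure, the estimate is unbiased, and the standard error already includes chance imbalance.

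**Conclusion.** The point holds as a free improvement. As printed, the Aim 1 and Aim 2 youth-outcome models leave any mean boy-girl difference in the residual, although the plan itself relies on outcome-explaining controls to raise power. The loss is modest and grows with the sex difference on each outcome; an outcome with no such difference loses nothing.

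Two stronger readings should be resisted. One is that the study is underpowered or Table 1 wrong: the table reproduces and is not overturned. The other is that the tabulated gain applies to every planned analysis. It belongs to models of outcome level, and the plan's change tests gain little or nothing. The sizes rest on the assumed 0.2 to 0.5 SD, the stated ICC of 0.30 and independence of siblings' sexes.

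**What to change.** In Model building and estimation, add youth sex to the control list as a fixed main effect in all Aim 1 and Aim 2 models of youth outcomes, and in the equations for youth-reported mediators (for example parental monitoring, differential treatment and sibling relationship quality). Amend the sentence under Administrative data and measures to say that youth sex is a covariate in Aims 1 and 2 as well as a moderator in Aim 3. The Aim 3 tests stay as they are.

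The cost is one degree of freedom per equation and a line of text. No new data are needed, and fixing the covariate now avoids a later choice made with results in view.

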**Background Characteristics**			
**1. Demographics**	All: Age, race/ethnicity; Parents: Income, work status, education completed, marital history	Survey	Survey
**2. Family structure**	Household and family structure; age, sex and living arrangements of children; (items asked depends on number of children).	Interview	
**3. Military status & history**	Dates, branch and component, pay grade;	Records	
**4. Civilian Employment**		Survey	
**5. Children’s health**	National Survey of Children’s Health [56]	Interview	
	Pubertal Development Scale(α = .78) [57]		Survey
**6. Personal characteristics**	Emotion regulation [58]	Survey	Survey
	Self-efficacy [59]	Interview	Survey
